### 3.4.2 Secondary Efficacy Endpoints

Pain score during the 72 hours following catheter insertion will be analyzed by a mixed model for repeated measures (MMRM), with random effects for intercept and time, fixed effects for treatment, sex, and intraoperative MMEs (<median, ≥median), and an unstructured covariance matrix.

The analysis of cumulative postoperative opioid use measured as MMEs from catheter insertion until discharge from hospital will be by the same methods as for the primary efficacy endpoint, including the joint model sensitivity analysis.

The analysis of incidence of delirium during the 72 hours following catheter insertion will be by logistic regression with fixed effects for treatment group, sex, and intraoperative MME (<median, ≥median). The treatment odds ratio (OR) and associated 95% confidence interval will be provided.

The analysis of Quality of Recovery-15 Scale administered 24-96 hours post-surgery will be by the same methods as for the primary efficacy endpoint.

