| Duration of Treatment | Treatment will be delivered for 48 hours post-catheter insertion.                                                                                                                                                                                                                                                                                                                                                                                                                                                                                                                                                                                                                                                                                                                                                                                                                                                                                                                                                                                                                                                                                                                                                                                                                                                                                                                                                                                                                                                                                                                                                                                                                                                                                                                                                                                                   |

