### 3.3 Secondary Endpoints

- Median pain score as measured by a standardized numeric rating scale over 72 hours following catheter insertion (measured at rest and with coughing q12hours  $\pm$  2 hours post-catheter insertion)
- Cumulative postoperative opioid use measured as Milligram Morphine Equivalent (MME) from catheter insertion until discharge from hospital

- Assessment for delirium BID for 72 hours following catheter insertion, as defined by the presence of one of the following criteria: Confusion Assessment Method (CAM) or CAM-ICU positive, or Intensive Care Delirium Screening Checklist (ICDSC) >3, or 3D-CAM, or 4AT  $\geq 4$ , or more than one dose of haloperidol or similar antipsychotic drug, or documented delirium by neurologist or psychiatrist consultation
- Quality of Recovery-15 Scale administered 24-96 hours post-surgery

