### *2.3.2 Secondary Efficacy Endpoints*

The secondary efficacy endpoints are to compare the 0.2% ropivacaine group with the placebo group in terms of the following:

- Pain score as measured by a standardized numeric rating scale during the 72 hours following catheter insertion
- Cumulative postoperative opioid use measured as MMEs from catheter insertion until discharge from hospital
- Incidence of delirium during the 72 hours following catheter insertion, as defined by the presence of one of the following criteria: Confusion Assessment Method (CAM) or CAM-ICU positive, or Intensive Care Delirium Screening Checklist (ICDSC) >3, or 3D-CAM, or 4AT  $\geq$ 4, or more than one dose of haloperidol or similar antipsychotic drug, or documented delirium by neurologist or psychiatrist consultation
- Quality of Recovery-15 Scale administered 24-96 hours post-surgery

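### The pain-score model in SAP 3.4.2 has no fixed time or treatment-by-time term, so its single treatment coefficient is not in general the 72-hour average difference, and its covariance wording fits two models

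*Combined protocol and SAP*

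**What the plan says.** SAP 3.4.2 gives the whole pain model in one sentence: a "mixed model for repeated measures (MMRM), with random effects for intercept and time, fixed effects for treatment, sex, and intraoperative MMEs" (split at the median), "and an unstructured covariance matrix". No other section adds a fixed time or treatment-by-time term, says how time is coded, or says which matrix is unstructured.

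The endpoint is worded differently in the two documents. Protocol 3.3 has "Median pain score as measured by a standardized numeric rating scale over 72 hours following catheter insertion", "measured at rest and with coughing q12hours". SAP 2.3.2 has "Pain score as measured by a standardized numeric rating scale during the 72 hours following catheter insertion", without a summary measure and without separating rest from cough.

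On exposure, the protocol synopsis says: "Treatment will be delivered for 48 hours post-catheter insertion". The last 24 hours of the pain window are therefore off infusion.

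**The concern.** A random slope without a fixed slope has mean zero. The model then says that average pain does not change over the three days after sternotomy, and any real change has to be absorbed as between-patient slope variance.

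The missing treatment-by-time term matters more. The window is 72 hours and the infusion lasts 48, so an effect that is present on infusion and fades afterwards is a natural possibility. One constant coefficient cannot show that. It is also not the plain average of the visit differences, because generalised least squares weights the visits according to the fitted covariance. What is estimated therefore depends on nuisance parameters and is not fixed in advance.

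The label MMRM, the random intercept and slope, and the unstructured matrix do not define a single model, so two programmers could fit different ones. The handling of rest and cough scores is also open, and SAP 3.1.5 makes no multiplicity adjustment. SAP 3.4.3 lets nausea and vomiting be analysed by the pain-score methods, so the gap may carry over.

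**Working it through.** **Plan figures.** The documents give no effect size, standard deviation (SD) or power for pain. The only sample size is for the primary endpoint (SAP 2.2.2). It reproduces: 2 × (1.960 + 1.282)² × 25² / 10² = 131.3, so 132 per group by the normal formula and 133 by the t-test. It is used below only as the number per arm.

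**Inputs.** From the documents: scores about every 12 hours over 72 hours, hence six nominal times, and a 48-hour infusion. Assumed, since the documents give no values: intercept SD 1.5, slope SD 0.15 per 12 hours, residual SD 1.2, time coded from catheter insertion. Six equally spaced times is itself a simplification, because Protocol 5.2 ties the first score to extubation and the second to the next study dose.

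**1. Covariance count at six visits.**
- Unstructured residual matrix: 6 × 7 / 2 = 21 parameters. A random intercept and slope add two variances and one covariance: 21 + 3 = 24. The rank of this parameterisation is 21, so 3 parameters are redundant.
- Unstructured random-effects matrix plus one residual variance: 3 + 1 = 4 parameters, rank 4. This is an ordinary random-coefficients model.

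**2. What the single coefficient estimates.** With complete data, the model's treatment coefficient is Σ wₖdₖ. Here dₖ is the treatment difference at visit k, w = V⁻¹1 / (1′V⁻¹1), V = ZGZ′ + σ²I, and Z has rows (1, k) for k = 1 to 6. Take d = 1 at 12 to 48 hours and 0 at 60 and 72 hours. The equally weighted mean is 4/6 = 0.667, and the model reports the sum of the first four weights.

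| Assumed intercept-slope correlation | Weights, 12 to 72 h | Reported effect | Relative to 0.667 |
|---|---|---|---|
| -0.5 | 0.12, 0.14, 0.16, 0.18, 0.19, 0.21 | 0.59 | -11% |
| -0.3 | 0.18, 0.18, 0.17, 0.16, 0.16, 0.15 | 0.69 | +4% |
| 0 | 0.27, 0.23, 0.19, 0.15, 0.10, 0.06 | 0.84 | +26% |
| +0.3 | 0.37, 0.29, 0.21, 0.13, 0.05, -0.03 | 0.99 | +48% |

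A separate REML simulation used other assumed values: 133 per arm, intercept SD 1.2, slope SD 0.4 per day, residual SD 1.3, correlation 0. The model as written gave 0.88 to 0.92 for the same true 0.667. With treatment-by-visit terms, the equally weighted contrast gave 0.65 to 0.68.

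**3. Effect of omitting fixed time.** In that simulation, a mean decline of 1 point per day raised the estimated slope variance to 0.80, against 0.21 with fixed visit effects. The treatment estimate did not move. Under the assumptions of step 2, adding a fixed linear time term also leaves the complete-data estimate unchanged to three decimals, for declines of 0, 0.25 and 0.5 points per 12 hours.

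**4. Type I error.** Under no effect with complete data, rejection was 6.0% in 250 simulations (Monte Carlo SE √(0.05 × 0.95 / 250) = 1.4 points), with or without fixed time. With the first score missing in 40% of placebo and 20% of active patients (assumed), the null estimate shifted by 0.035 points and rejection was 6.8%, against 4.4% with fixed time. That gap is compatible with simulation error.

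**The case against.** The best defence has four parts.

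- **The covariance sentence can be read sensibly.** Unstructured may refer to the two random effects just named. The model is then standard and identifiable, and only the MMRM label is loose. This stands: the text is ambiguous, not certainly wrong. A reader might infer that the model cannot be fitted. The documents do not support that, because the over-parameterised reading is only one of two. Even there the marginal covariance and the fixed effects remain estimable, and no failed fit has been shown.
- **The missing fixed time term hardly affects the treatment comparison.** This stands for complete data, as step 3 shows. With unequal first assessments the shift is small.
- **SAP 2.1.2 asks only about pain over 72 hours, so one overall coefficient is legitimate.** This stands in part. No objective asks for a time course. But an overall comparison needs a stated weighting, and the model as written leaves that to the data.
- **The size rests on invented variances.** This stands as a limit on any single figure, which is why a range is given.

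The omission is unlikely to be shorthand, since SAP 3.4.4 names its interaction explicitly where it wants one.

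**Conclusion.** The point holds as a specification gap in one secondary endpoint. The listed model forces a zero mean slope, cannot show a fade after 48 hours, and gives a treatment coefficient that is not in general the 72-hour mean difference.

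In the illustration the discrepancy runs from 0.59 - 0.67 = -0.08 to 0.99 - 0.67 = +0.32 points. It rests on the assumed standard deviations, the assumed step-shaped effect, six complete visits and the random-coefficients reading. If the true effect is constant over 72 hours, the discrepancy vanishes, because the weights sum to one.

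Two stronger inferences are tempting. One is that the model overweights early scores and so flatters the block. That is not a property of the model: at a correlation of -0.5 the later visits weigh more and the effect is understated. The other is that the treatment test is invalid. The simulations show roughly nominal type I error. The primary ANCOVA and the sample size are not touched.

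**What to change.** Amend SAP 3.4.2 before database lock, which is when SAP Section 1 says the plan will be final:

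- Fixed effects for treatment, nominal assessment time (categorical), treatment-by-time, sex and intraoperative MME category. Define the nominal times from catheter insertion.
- An unstructured within-patient residual covariance and no random effects.
- The equally weighted 72-hour treatment contrast as the reported endpoint, with the time-specific contrasts as description.
- Separate models for rest and cough scores.
- A statement that reconciles this analysis with the protocol's median pain score, in one document or the other.
- If nausea and vomiting scores are to use the pain model, a statement that the revised model applies.

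The cost is SAP wording and standard code. At six visits the mean model gains 5 time and 5 interaction terms, and the covariance has 21 parameters instead of the 4 of the random-coefficients reading. In the simulation, which kept the random-slope covariance, the standard error of the equally weighted contrast was 0.183, against 0.177 for the single coefficient, about 3% larger (0.183 / 0.177 = 1.03). No change to recruitment, data collection or the primary analysis is needed.

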### 3.4.3 Exploratory Efficacy Endpoints

The analyses of time-to-event exploratory efficacy endpoints will be by proportional hazards models with fixed effects for treatment, sex, and intraoperative MMEs (<median, ≥median). The treatment hazard ratio (HR) and associated 95% CI will be provided. A cause-specific approach for competing terminal events (i.e., deaths) will be applied by censoring participants at the time of death. Cumulative incidences by treatment group will be estimated by Kaplan-Meier methods.

The analyses of incidence of postoperative nausea or vomiting will be by the same methods as pain score or delirium.

Opioid requirements post-discharge will be summarized by descriptive statistics.

The analyses of chronic post sternotomy pain/disability and patient reported outcomes assessed with the McGill Pain Questionnaire (3 months) and PROMIS 29 score (6 weeks, 3 months) will be by the same methods as for the primary efficacy endpoint.

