## **7. Statistical Analysis and Sample Size Calculation**

For the primary analysis, we will perform linear regression, adjusted for sex (clinical stratification factor) and intraoperative opioid MME to assess the comparison between trial groups, with a P-value threshold of 0.05 being considered significant. If residuals indicate substantial violations of the linear regression assumptions, alternate methods will be attempted, such as analyzing log-transformed data, using bootstrap hypothesis testing or two-sample t-tests without equal variance. A modified intention-to-treat analysis will be employed, including only patients in whom a block catheter was placed, and a dose of study drug was administered. The time-to-event outcomes will be modelled simultaneously using a multistate framework. This approach will handle competing risks, such as death, and treat other non-fatal events, that could be related to each other, as intercurrent events. Sensitivity analyses using complete intention-to-treat and per protocol populations will also be conducted. Categorical data will be summarized by frequencies and percentages, and continuous variables by means and standard deviations (plus medians and interquartile ranges for non-symmetric data).

In order to detect a mean difference of 10 MMEs, assuming a standard deviation of 25 and an alpha value of 0.05, a sample size of 133 participants per group would be required to provide a power of 90%. Assuming an attrition rate of 25%, approximately 340 patients will need to be randomized for the primary modified intention-to-treat analysis.

Pre-specified subgroup analyses of the primary outcome include:

- Age
- Race/Ethnicity
- Sex/Gender
- Diabetes status
- BMI
- Type of operation
- Site

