### *2.3.3 Exploratory Efficacy Endpoints*

The exploratory efficacy endpoints are to compare the 0.2% ropivacaine group with the placebo group in terms of the following:

- Time from catheter insertion to extubation
- Time from catheter insertion to first opioid analgesic provision following extubation
- Time from catheter insertion to mobilization
- ICU and hospital LOS

- Incidence of postoperative nausea or vomiting, measured via a 10-point visual analogue scale twice daily (BID) and antiemetic medication requirements during the 72 hours following catheter insertion
- Opioid requirements post-discharge as assessed by prescriptions provided at time of discharge and during post-discharge follow-up visit using both patient health record and direct patient recounting
- Chronic post sternotomy pain/disability and patient reported outcomes assessed with the McGill Pain Questionnaire and PROMIS 29 score

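### SAP 3.4.3 estimates cumulative incidences by Kaplan-Meier with deaths censored, which overstates them whenever a death precedes a later event; only the descriptive exploratory curves are affected

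*Combined protocol and SAP*

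**What the plan says.** SAP 3.4.3 analyses the time-to-event exploratory endpoints by proportional hazards models with treatment, sex and dichotomised intraoperative MMEs as fixed effects, and reports a hazard ratio with its 95% CI. On death it says: "A cause-specific approach for competing terminal events (i.e., deaths) will be applied by censoring participants at the time of death". The next sentence is: "Cumulative incidences by treatment group will be estimated by Kaplan-Meier methods". The SAP names no competing-risk estimator of cumulative incidence anywhere.

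The endpoints are listed in SAP 2.3.3. Three are worded as times from catheter insertion: to extubation, to first opioid after extubation, and to mobilisation. A fourth entry, "ICU and hospital LOS", is not labelled as time-to-event, and SAP 3.4.3 names no separate method for it.

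Protocol section 7 plans something different for the same class of outcomes. They are to be modelled jointly in a multistate framework, of which it says: "This approach will handle competing risks, such as death". Other non-fatal events are to be treated there as intercurrent. The SAP does not mention this framework or explain the change.

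**The concern.** The two adjacent SAP sentences serve different targets. A cause-specific hazard is the event rate among patients still alive and event-free, so censoring at death is the right way to estimate it. A cumulative incidence is the proportion of all patients who have had the event by a given time. A patient who dies first never has it and must stay in the denominator. Kaplan-Meier with deaths censored instead passes that patient's probability on to the survivors, as though extubation or mobilisation were still to come.

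The SAP calls the result a cumulative incidence, so readers will take the percentages as observed proportions. These would be too high, and by different amounts in the two arms if mortality differs.

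**Working it through.** **Inputs from the documents.** Estimator and handling of death: SAP 3.4.3. Endpoints: SAP 2.3.3. About 340 randomised 1:1, so 340/2 = 170 per arm: SAP 2.2.1. The documents give no mortality, event probability or median time for these endpoints, so there is no stated figure to reproduce. All rates and medians below are assumptions.

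**Direction and bound (no mortality assumption needed).** At each time u, let r be the number at risk, d1 the events and d2 the deaths.
- Event-only Kaplan-Meier: S_e = Π(1 − d1/r).
- Survival free of both event and death: S = Π(1 − (d1+d2)/r), so S ≤ S_e.
- 1 − KM rises by S_e(u−)·d1/r at each event time. Aalen-Johansen rises by S(u−)·d1/r. The first is never smaller, and it is strictly larger at any event after a death.
- The incidences of event and of death as first event, F_e and F_d, add up to 1 − S. Since 1 − S_e ≤ 1 − S = F_e + F_d, the excess (1 − S_e) − F_e is at most F_d, the probability of dying before the event by that time.

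**Count example.** Take an arm of 170 with 165 events, then 4 deaths, then 1 event. The last patient at risk has the event, so 1 − KM = 100%. Aalen-Johansen gives 166/170 = 97.6%. The excess is 4/170 = 2.4 points, exactly the bound.

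**Size under constant hazards.** Let λ = ln 2/median, let q be the probability of dying before the event, and let μ = λq/(1−q). Then 1 − KM(t) = 1 − exp(−λt), and the cumulative incidence is F(t) = (1−q)[1 − exp(−(λ+μ)t)].

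Hospital discharge, assumed median 6 days (λ = 0.1155 per day):

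| q | Day | 1 − KM | Cumulative incidence | Excess (points) |
|---|---|---|---|---|
| 2% | 10 | 68.5% | 0.98 × (1 − e^−1.179) = 67.9% | 0.7 |
| 2% | 40 | 99.0% | 0.98 × (1 − e^−4.715) = 97.1% | 1.9 |
| 4% | 10 | 68.5% | 0.96 × (1 − e^−1.203) = 67.2% | 1.3 |
| 4% | 40 | 99.0% | 0.96 × (1 − e^−4.814) = 95.2% | 3.8 |

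Excesses are taken before rounding.

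Endpoints worded as times, at 72 hours:

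| Endpoint (assumed median) | 1 − KM | Excess, q = 1% | q = 2% | q = 5% |
|---|---|---|---|---|
| Extubation (8 h) | 99.8% | 1.0 | 2.0 | 4.9 |
| Mobilisation (30 h) | 81.1% | 0.5 | 1.0 | 2.5 |

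Here q counts only deaths before extubation or before mobilisation. In-hospital mortality must not be put in its place.

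**Check with the estimators themselves.** In simulated arms of 170 (discharge by day 30, 6-day median), the mean excess was 0.9, 1.8 and 4.4 points at q = 1%, 2% and 5%. The formula gives 0.9, 1.7 and 4.4.

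**Unequal mortality.** With equal discharge hazards but q = 1% in one arm and 3% in the other, 1 − KM at day 30 is 96.9% in both arms. The cumulative incidences are 96.0% and 94.3%, so Kaplan-Meier hides a 1.7-point difference.

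**The case against.** The strongest case on the other side is that the effect is small and touches no inference.

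- **Few competing deaths are likely.** Protocol 4.2 excludes emergency procedures, clinical instability, redo sternotomy and endocarditis. Catheters go in after skin closure, and the mITT population requires a placed catheter and a dose, so intraoperative deaths before that point drop out. Only deaths before the event compete. This stands: the 1% to 5% range is illustrative, and at 1% the excess is about a point or less.
- **Sampling error is larger over the informative part of the curve.** At 68% with 170 patients the standard error is √(0.68 × 0.32/170) = 3.6 points, against a bias of 0.7 or 1.3. The bias exceeds it only in the far tail: at day 40 with 2% mortality it is 1.9 points, against √(0.971 × 0.029/170) = 1.3. This stands as to size. It does not make the estimator right.
- **The treatment comparison is the hazard ratio.** This also stands. The curves are descriptive and the endpoints exploratory.

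Three stronger readings are tempting. A reader might infer that the SAP ignores death altogether. It does not: it names death as competing, and its cause-specific model is sound. A reader might infer that 1 − KM always climbs to 100%. It reaches 100% only if the last patient at risk has the event. A reader might take it as settled that the length-of-stay curves are biased. The SAP never says that length of stay is analysed as time-to-event, so that part is conditional.

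**Conclusion.** The concern holds for the cumulative incidence curves. As written, the SAP rule overstates the incidence of extubation, first opioid after extubation and mobilisation whenever a death precedes a later event, and nothing elsewhere in the SAP repairs it. It applies to ICU and hospital discharge only if length of stay is analysed as time-to-event.

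The direction and the upper bound do not depend on any assumed rate. The size does: the discharge figures of 0.7 to 1.9 points (2% mortality) and 1.3 to 3.8 points (4%) rest on constant hazards and an assumed 6-day median. The error may differ by arm if mortality differs.

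A reader might go on to doubt the hazard ratios or the trial's main result. The documents give no ground for that, because the cause-specific model is unaffected and the primary endpoint does not use this method. Separately, the SAP and protocol section 7 describe different methods for these outcomes, and the two sections need to be reconciled whatever the size of the bias.

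**What to change.** 1. Replace the Kaplan-Meier sentence in SAP 3.4.3 with wording such as: *The cumulative incidence of each event in each arm will be estimated by the Aalen-Johansen method, with death before the event as a competing event.*
2. Keep the cause-specific proportional hazards model with censoring at death.
3. State whether ICU and hospital length of stay are analysed as time-to-event. If so, the same estimator applies.
4. Reconcile the SAP with protocol section 7: either restore the multistate framework or record that it was dropped and why. Aalen-Johansen with death as the only competitor corrects the curves, but it does not deliver the joint model of non-fatal events that the protocol describes.

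Gray's test is optional. It compares cumulative incidence functions, a different hypothesis from the cause-specific hazard ratio, and the correction does not need it.

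Items 1 to 3 cost a few lines of SAP text and a small programming change. They need no new data and do not affect trial conduct. Item 4 costs a short explanation if the framework is dropped, and more analysis work if it is restored.

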### 3.4 Tertiary (exploratory) Endpoints

- Time from catheter insertion to extubation
- Time from catheter insertion to first opioid analgesic provision following extubation
- Time from catheter insertion to mobilization
- ICU and hospital LOS
- Postoperative nausea and vomiting, measured via a 10-point visual analogue scale BID and antiemetic medication requirements up to 72 hours following catheter insertion
- Opioid requirements post-discharge as assessed by prescriptions provided at time of discharge and during post-discharge follow-up visit using both patient health record and direct patient recounting
- Chronic post sternotomy pain/disability and patient reported outcomes assessed at 3 months  $\pm$  4 weeks from surgery with McGill Pain Questionnaire as well as at 6 weeks  $\pm$  2 weeks and 3 months  $\pm$  4 weeks with the change in PROMIS 29 score (Attempts to obtain the 3-month data can continue for up to 6 months post-surgery before it will be considered a protocol deviation or the participant deemed lost-to-follow-up)

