### 5.2 Study Visits

#### *Visit S: Screening*

- Written informed consent
- Determination of eligibility
- Demographics, medical history, baseline medications including doses
- Physical examination, height and weight assessment, BMI
- Vital signs
- Laboratory assessments: CBC, creatinine/eGFR, electrolytes, coagulation testing
- Preoperative PROMIS 29 Score

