- Attempts to obtain the 3-month data can continue for up to 6 months post-surgery before it will be considered a protocol deviation or the participant deemed lost-to-follow-up

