##### 3.1.2 Analysis Visits

Scheduled visits will be assigned to analysis visits as recorded on the case report form (CRF).

For each analysis visit, if a scheduled visit occurs within the analysis day window, then the measurement from this scheduled visit will be used. If no scheduled visit occurs or laboratory results of the scheduled visit were unreportable, the unscheduled measurement closest to the target day will be used. If measurements are equidistant to the target day, the later will be used.

| Analysis Visit             | Target Analysis Day | Low Analysis Day | High Analysis Day |
|-----------------------------------|----------------------------|-------------------------|--------------------------|
| Day 0 (day of catheter insertion) | 0                          | 0                       | 0                        |
| Day 42 (phone call visit)         | 42                         | 28                      | 56                       |
| Day 91 (phone call visit)         | 91                         | 63                      | 119                      |

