##### 3.1.3 Definition of Baseline

Baseline is defined as the last measurement prior to the first dose of study treatment, unless otherwise stated.

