The analysis of covariance (ANCOVA) model with a fixed effects for treatment group, sex, BMI and intraoperative MMEs ( $<$ median,  $\geq$ median) will be used to analyze the primary efficacy endpoint. The least squares (LS) mean, standard errors, and 2-sided 95% confidence intervals (CIs) for each treatment group and for the mean difference compared to placebo will be estimated. The model will be fit assuming unequal variances for each treatment group. If substantial deviations from the model assumptions are observed, then supportive analyses, such as robust regression, non-parametric analyses, etc. will be considered. Missing values of predictors will either be imputed by the overall mean or most frequent category.

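### The SAP's PROMIS-29 model leaves out the preoperative score that the protocol collects and does not analyse the protocol's change endpoint; which rule governs 3-month calls after Day 119 is also left open

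*Combined protocol and SAP*

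**What the plan says.** **Baseline and endpoint.** Protocol section 5.2, screening visit, lists "Preoperative PROMIS 29 Score". Protocol section 3.4 defines the patient-reported endpoint at 6 weeks and 3 months "with the change in PROMIS 29 score". SAP section 2.3.3 names it as "patient reported outcomes assessed with the McGill Pain Questionnaire and PROMIS 29 score", with no mention of change.

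**Model.** SAP section 3.4.3 says that analyses of the McGill questionnaire and the "PROMIS 29 score (6 weeks, 3 months) will be by the same methods as for the primary efficacy endpoint". The primary analysis in SAP section 3.4.1 is an ANCOVA with "fixed effects for treatment group, sex, BMI and intraoperative MMEs", the last split at the median. SAP section 3.1.3 does define a baseline ("Baseline is defined as the last measurement prior to the first dose of study treatment, unless otherwise stated"), and section 3.3.3 tabulates baseline PROMIS-29. Neither carries the score into a model.

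**Timing.** SAP section 3.1.2 first assigns scheduled visits by their CRF label. It then says that a scheduled visit inside the analysis-day window is the one used, and gives the 3-month visit a window of Day 63 to Day 119. Protocol section 5.2, Visit P2, says: "Attempts to obtain the 3-month data can continue for up to 6 months post-surgery"; only after that is a deviation or loss to follow-up declared. SAP section 2.2.1 itself describes the later contact as being at 3 to 6 months.

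**The concern.** The primary endpoint, cumulative opioid use after catheter insertion, has no preoperative counterpart. Its model therefore has no place for a baseline value, and borrowing it unchanged for PROMIS-29 loses one. A patient's preoperative score will usually predict the follow-up score. Leaving it out puts that predictable variation into the residual and widens the confidence interval.

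There is also a consistency problem. The protocol promises an analysis of change; the SAP, read literally, analyses the follow-up score. A report written to the SAP would not deliver the protocol's endpoint.

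The timing question is smaller. If the two rules in SAP 3.1.2 give different answers for a late call, someone must choose between them. Made after the data are seen, that choice decides which patients count in the 3-month PROMIS-29 and McGill analyses. SAP section 3.1.6 rules out imputing missing efficacy data, so a patient whose call is not used leaves that analysis.

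**Working it through.** **1. The plan's own figure.** The documents give no SD, correlation or power for PROMIS-29. The only sample-size figure is for the primary endpoint: difference 10 MME, SD 25, two-sided 5%, power 90%. The normal approximation 2(z₀.₉₇₅ + z₀.₉₀)²(25/10)² is just over 131, so 132 per group. The exact t-based calculation gives power 0.8993 at 132 and 0.9015 at 133. The stated 133 per group is reproduced.

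**2. What is in the PROMIS-29 model.**

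| Item | Protocol | SAP |
|---|---|---|
| Preoperative score | Collected (5.2, screening) | Tabulated (3.3.3), not modelled |
| Endpoint | Change (3.4) | Score (2.3.3) |
| Model terms | Not stated for PROMIS-29 | Treatment, sex, BMI, intraoperative MME (3.4.3 via 3.4.1) |

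**3. Gain from adding the baseline score.** Let r be the correlation between baseline and follow-up score that remains after sex, BMI and intraoperative MME. It is not in the documents; 0.3 to 0.7 is an assumption. Take equal variances at the two times.

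- Against the follow-up score alone: SE ratio = √(1 − r²); equivalent sample size = 1/(1 − r²).
- Unadjusted change against the follow-up score: SE ratio = √(2(1 − r)).
- Adjusted against unadjusted change: variance ratio (1 − r²)/(2(1 − r)) = (1 + r)/2, so SE ratio = √((1 + r)/2).

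| r | Adjusted vs follow-up score | Equivalent N | Unadjusted change vs follow-up score | Adjusted vs unadjusted change |
|---|---|---|---|---|
| 0.3 | 0.954 | 1.10 | 1.183 | 0.806 |
| 0.5 | 0.866 | 1.33 | 1.000 | 0.866 |
| 0.6 | 0.800 | 1.56 | 0.894 | 0.894 |
| 0.7 | 0.714 | 1.96 | 0.775 | 0.922 |

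The SE falls by about 5% at r = 0.3 and 29% at r = 0.7 against the follow-up score. If the comparator is instead an unadjusted change score, the gain is smaller once r exceeds 0.5: about 11% at r = 0.6. Below r = 0.5, an unadjusted change score is less precise than the follow-up score alone.

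**4. In terms of power.** Take 340 × 0.75 = 255 evaluable patients and, as an assumption, an effect of 0.3 SD. Power is 0.67 without the baseline score, and 0.71, 0.79 and 0.92 with it at r = 0.3, 0.5 and 0.7.

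**5. Change and follow-up score agree once baseline is in.** If Y − B = a + τT + βB + other terms, then Y = a + τT + (β + 1)B + other terms. The treatment effect τ, its SE and the residuals are identical when the same patients and baseline values are used.

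**6. Windows.** 42 ± 14 gives Days 28 to 56, and 91 ± 28 gives Days 63 to 119. Both match the protocol's visit windows. Six months is about Day 183 (365.25/2 = 182.6). For a 3-month call after Day 119, the CRF-label rule keeps it; the window rule, read strictly, does not select it. The share of such calls is not given. If it were 5%, 10%, 20% or 30% (assumption) and the calls were not used, the SE would rise by 1/√(1 − f) − 1, which is 2.6%, 5.4%, 11.8% or 19.5%.

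**The case against.** The strongest reply is that PROMIS-29 is one of many exploratory endpoints, that it is unpowered, and that randomisation protects the comparison without a baseline term. All of that stands. A reader might infer bias from the missing covariate, but the documents do not support this: the loss is in efficiency and in agreement with the protocol. Nor is the model unadjusted, since sex, BMI and intraoperative MME are already in it. That is why r must be the correlation remaining after those terms, and why the size of the gain is only a range.

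A reader might also infer that the SAP drops 3-month calls made after Day 119. The text does not settle that. The CRF-label rule in the same section would keep such a call, nothing says that a late scheduled call is discarded, and the 3 to 6 month wording in SAP 2.2.1 leans towards keeping it. Counting the days between Day 119 and about Day 183 measures calendar time, not lost patients. Nor do the documents show that late callers differ from the rest.

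Days 57 to 62 belong to no window and could be taken for a SAP error. They lie outside both protocol visit windows, which the SAP copies exactly, so no correction is needed.

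Finally, the protocol still labels the endpoint as 3 months ± 4 weeks. It is therefore arguable that Day 119 should bound the main analysis. The documents do not decide this, so the request is only that the choice be stated.

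**Conclusion.** The baseline point holds. The preoperative PROMIS-29 score is collected, defined as a baseline and tabulated, but it is absent from the model, and the protocol's change endpoint is not what the SAP analyses. The gain from including it is real for any non-zero correlation. Its size, a 5% to 29% smaller SE or 1.10 to 1.96 times the sample size against the follow-up score alone, rests on an assumed r of 0.3 to 0.7. The point does not extend to the McGill questionnaire, for which no preoperative score is listed.

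The timing point holds only as an unresolved conflict between two assignment rules. Its effect cannot be sized without the share of late calls.

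Both points concern exploratory endpoints. The primary conclusion is unaffected.

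**What to change.** - In SAP section 3.4.3, add the preoperative PROMIS-29 score as a continuous covariate in each PROMIS-29 model at 6 weeks and 3 months, alongside the existing terms. State that the treatment effect is then the same for change and for follow-up score, so the protocol's endpoint is met. Do not substitute an unadjusted change score.
- Say that a missing preoperative score is handled by the rule for missing predictors already in SAP section 3.4.1. The equivalence of change and follow-up score holds if the same patients and baseline values are used.
- Leave the McGill model as it is.
- In SAP section 3.1.2, state before database lock whether the CRF label or the Day 63 to 119 window governs a 3-month call made after Day 119. Run the other as a sensitivity analysis, and report how many calls are affected in each group.

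The cost is one covariate, a few sentences of SAP text and one additional sensitivity run. No new data are needed. If the CRF-label rule is chosen, the 3-month assessments will vary somewhat more in timing; the sensitivity analysis shows whether that matters.
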